#### Secondary outcome analyses

A similar modeling strategy to that described above for 7-day point prevalence abstinence will be used to assess between group differences in 30-day point prevalence abstinence and continuous abstinence. We will estimate the effect of interventions on time to first lapse (i.e., first puff) and first relapse (i.e., smoking 7 consecutive days or in two consecutive 7-day periods) using survival analysis [93]. Each participant contributes two outcome variables to the model: T*_i_, time to first lapse/relapse and C_i_, censoring time (T*_i_ < C_i_ for those who lapse/relapse before the end-of-observation and T*_i_ > C_i_ for those who don’t lapse/relapse before end-of-observation or discontinue the study protocol before lapsing/relapsing). The response is considered to be min {T*_i_, C_i_}. Using a Cox model [94] , we can write the hazard function (which can be thought of as the number of lapses/relapses per participant-day of follow-up time) as a function of a baseline hazard rate λ_0_(t) and covariates X(t), including intervention assignment.

Parallel longitudinal mixed effects regression models to those used to evaluate between group differences in PHQ-9 will be used to evaluate changes CESD-10, PANAS, SHAPS, PSS, SF-12, and DASI.

We will test the effect of BAT-CS versus control on the time to occurrence of MACE and all-cause mortality over the 36-month follow-up (see Fig. 2). Time to event data will be modeled using a similar survival analysis method to that described above, but importantly, will also control for duration of follow-up as this will differ by participant and will likely be associated with the outcome. We will conduct separate survival analyses for MACE and all-cause mortality but will also analyze a composite of both to maximize power.

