## Methods

### Study design overview

324 ACS patients who smoke will be recruited and randomly assigned to 12 weeks of either Behavioral Activation Treatment for Cardiac Smokers (BAT-CS; smoking cessation and BA based mood management counseling) or a control condition (smoking cessation and health education) that fully controls for BA contact time (see Fig. 2). All participants will be offered 8 weeks of the nicotine patch if medically appropriate. All counseling in both conditions will be provided by tobacco treatment specialists over 12 weeks post-discharge. Comprehensive assessments completed by blind to condition assessors will occur at end-of-treatment (12 weeks after discharge) and 6, 9, and 12 months after discharge. Major Adverse Cardiac Events (MACE; i.e., hospitalization for unstable angina, urgent coronary revascularization, myocardial infarction) and all-cause mortality will be tracked through the end of the study for up to 36 months (see Table 1 and Fig. 2). Recruitment began on 1/22/2018. This protocol is presented consistent with SPIRIT guidelines (see additional file 1).

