### Outcome assessments

Comprehensive outcomes assessments will be conducted in person, by phone, or using video conference at end of treatment (12 weeks after discharge) and 6, 9, and 12 months after discharge. Abbreviated phone assessments will be conducted by phone at 18-, 24-, 30-, and 36-months post discharge. Assessments through 12 months post-discharge will include biochemical verification of self-reported smoking status. Abbreviated assessments after 12 months will only collect self-reported smoking status.

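### The survival models for MACE, mortality and their composite adjust for an undefined duration of follow-up, which is redundant on one reading and on another is the outcome itself

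*Protocol article*

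**What the plan says.** The Secondary outcome analyses section of the protocol article first sets out a Cox model for lapse and relapse. The response is the smaller of event time T* and censoring time C, and the hazard is explained as something "which can be thought of as the number of lapses/relapses per participant-day of follow-up time". For the cardiac events it then says: "Time to event data will be modeled using a similar survival analysis method to that described above", and adds, as an important difference, that the model "will also control for duration of follow-up as this will differ by participant and will likely be associated with the outcome".

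The rule covers three endpoints: "We will conduct separate survival analyses for MACE and all-cause mortality but will also analyze a composite of both to maximize power".

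The article does not say what duration of follow-up means. Two other places bear on it:

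- Study design overview says that MACE and "all-cause mortality will be tracked through the end of the study for up to 36 months". Available follow-up can therefore vary with enrolment date.
- Outcome assessments says: "Abbreviated phone assessments will be conducted by phone at 18-, 24-, 30-, and 36-months post discharge". Nothing there, or in Table 1, ends contact after a non-fatal MACE.

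**The concern.** A Cox model compares each participant who has an event with those still at risk at that moment. Participants with shorter follow-up leave the risk set when they are censored. That follow-up differs between participants is therefore what the model already allows for, and is not a reason to add a covariate.

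Adding one can do harm. If the covariate is the time actually observed, it is known only once the event or censoring has happened, and for participants with events it equals the outcome. An analyst who followed the sentence literally would get a model that cannot be fitted. A workaround chosen at that stage would be a post hoc decision, and one that coarsens or constrains the term would tend to hide a treatment effect. The sentence governs every event analysis under Aim II.

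**Working it through.** The protocol gives no event count, hazard ratio (HR) or power for MACE or mortality, so there is no planned figure to reproduce. The check is algebra for the observed-time reading, then simulation for each reading.

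**1. Observed time as covariate (algebra).** Let g be the arm, β its coefficient, t the observed time min(T*, C), and γ the coefficient of t entered as a covariate. The contribution of an event at t_i is

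exp(βg_i + γt_i) / Σ_{j: t_j ≥ t_i} exp(βg_j + γt_j) = 1 / Σ_j exp[β(g_j − g_i) + γ(t_j − t_i)].

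Every difference t_j − t_i in the risk set is zero or positive. As γ → −∞, every term except that of participant i goes to zero (no ties) and the contribution goes to 1. The log partial likelihood climbs to its upper bound of 0 whatever β is. So γ has no finite estimate and, in the limit, β is not identified. No event rate is assumed here.

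For all-cause mortality, total time in study is also time to death or censoring, so the same result holds.

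**2. Numerical illustration.** One simulated data set, n = 324, true HR 0.7:

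| Slope γ per month | log PL at HR 1 | log PL at HR 0.7 | Difference (0.7 minus 1) |
|---|---|---|---|
| 0 | −416.540 | −413.985 | 2.555 |
| −1 | −173.271 | −174.000 | −0.729 |
| −100 | −5.671 | −5.896 | −0.225 |
| −1000 | −0.119 | −0.122 | −0.003 |

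The information about treatment disappears as the slope falls. In simulation, all 200 fits failed in every scenario.

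**3. Observed time with the slope held fixed**, as a stand-in for a constrained fit. From the protocol: n = 324 and follow-up of up to 36 months. Assumed: 1:1 allocation, 36-month control risk of 35% for the composite, available follow-up min(36, uniform 12 to 48) months, random loss of 15% per year, 200 trials per row. Cells give median HR and rejection rate.

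| True HR | No covariate | γ = −0.1 | γ = −0.3 | γ = −1.0 |
|---|---|---|---|---|
| 0.5 | 0.484 (73%) | 0.528 (66%) | 0.557 (58%) | 0.597 (44%) |
| 0.7 | 0.686 (31%) | 0.709 (25%) | 0.744 (20%) | 0.770 (13%) |

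Coarsening works in the same direction. With observed time rounded to 6 months (30% control risk, follow-up 18 to 36 months, both assumed), a true HR of 0.70 was estimated as 0.70 without the term and 0.83 with it, and power fell from 27% to 10%. Another run gave a move from 0.70 to 0.79. The rounding is an assumption and appears nowhere in the article.

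**4. Total time in study, continuing after a non-fatal MACE.**

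- MACE: 0.504 with the term against 0.503 without (true 0.5), and 0.708 against 0.709 (true 0.7). With the death hazard raised 8-fold after MACE: 0.486 against 0.488 (true 0.5).
- Composite: under one set of assumed risks (30% MACE, 12% death), 0.478 became 0.486 and 0.706 became 0.726, with no change in rejection (80% and 32%). Under another (25% MACE, 12% death), 0.49 became 0.52 and 0.70 became 0.72, with power falling from 82% to 72% and from 33% to 27%.

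**5. Available follow-up fixed by enrolment date.** Composite HRs with and without the term were 0.496 and 0.496 (true 0.5), and 0.713 and 0.716 (true 0.7). Nothing is lost or gained.

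**The case against.** A reader might infer that the covariate is certainly determined by the event in all three models, so that every Aim II hazard ratio is driven towards 1 or cannot be estimated. The document does not support that. It never equates duration of follow-up with the observed event or censoring time. Study design overview supplies an innocent meaning: participants enrolled later have less follow-up available before the study closes. That quantity is fixed at enrolment, and adjusting for it leaves the hazard ratio unchanged. Contacts also run to 36 months with nothing to stop them after a non-fatal MACE, so on the time-in-study reading the breakdown is confined to mortality. These points stand, and they limit the scope of the concern.

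It also stands that an outright failure to converge would be noticed rather than silently reported, that the size of any attenuation rests on assumed event rates and on a coarsening or constraint the article does not mention, and that the endpoints are secondary.

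A further objection is that a journal article leaves covariate definitions to the analysis plan. That answers only part of the point. The article does not merely omit a definition. It states a rule and gives a reason for it, and the reason is mistaken because differing follow-up is already handled by censoring. No reading gives grounds for keeping the term.

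**Conclusion.** The point holds in limited form. The covariate is unnecessary on every reading and undefined as written.

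- **Observed time, or total time in study for mortality:** the model has no finite estimate. This is algebraic. Constrained or coarsened versions generally pull the MACE and composite hazard ratios towards 1. In the fixed-slope composite runs, 0.484 moved to between 0.528 and 0.597, and 0.686 to between 0.709 and 0.770. These sizes depend on the assumed event rates, accrual and loss, and on the constraint chosen.
- **Total time in study:** MACE is essentially unchanged, and the composite moves by about 0.01 to 0.03 on the hazard ratio scale.
- **Available follow-up fixed by enrolment date:** harmless and redundant.

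Only the Aim II event analyses are affected. Aim I and the Power section show that the trial is powered for mood and 7-day abstinence, not for cardiac events. The primary analyses are untouched. This is a cheap correction to a secondary analysis and not a threat to the trial's main conclusions.

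**What to change.** Delete the duration-of-follow-up covariate from the MACE, mortality and composite models. State instead that unequal follow-up is handled by right censoring at the earliest of last confirmed event-free contact, study end and 36 months. If the worry is that event risk or care changed over the recruitment period, adjust only for enrolment date or period, which is fixed before randomisation.

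The cost is one sentence of analysis wording. It needs no new data and no change to design or sample size. It should be settled before outcome data are examined by arm, so that no workaround has to be chosen after a failed fit.

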#### Mediator analyses

We will explore potential mediators of intervention effects on depressed mood and smoking cessation. We will consider two mediation models: Model 1 will consider engagement in pleasant and valued activities (i.e., BADS, PES) as mediators of the intervention effect on depressed mood; Model 2 will consider depressed mood and engagement in pleasant/valued activities (i.e., BADS, PES) as potential mediators of the intervention effect on smoking cessation. For Model 1, we will use a multiple mediation approach, in which all potential mediators are tested simultaneously using a product of coefficients method [95] with bootstrapped standard errors (5000 samples with replacement). We will estimate the path coefficients (*a* path: effects of intervention on changes in mediators over time and *b* path: effects of changes in the mediators on depression over time, controlling for baseline), as well as the indirect effect of intervention (*ab* path: effect of intervention on depression through the mediators). Interest is in estimating the path coefficients, effect sizes, and confidence intervals, rather than strict hypothesis testing. In Model 2, we will use a similar approach to estimate the path coefficients and indirect effects of intervention on smoking cessation over time through changes in depressed mood and engagement in pleasant/valued activities over time.

#### Interaction of depressed mood and smoking over time analyses

Finally, we will explore the temporal interaction of smoking and multiple aspects of mood over 12 months post-ACS using an autoregressive, cross-lagged regression model, in which trajectories of mood, smoking status and their cross-lagged effects are studied simultaneously over time and effects of BAT-CS versus control on these relationships can be estimated.

##### Missing data

All analyses (other than the per protocol analyses detailed above) will be on the intent-to-treat sample (everyone randomized will be included in the final analysis) under various assumptions about the missing data mechanism. Sensitivity to these assumptions will be tested. Specifically, we will gather follow-up information and reasons for dropout regardless of protocol completion. We will compare the robustness of our findings using two statistical approaches for handling missing data. First, we will use inverse probability weighting with propensity scores. This is a two-step method: (1) using logistic regression, the probability of missingness is modeled as a function of baseline covariates and baseline values of the outcome and (2) the inverse of the propensity scores (predicted probabilities of dropout from the first step) serve as weights in our regression model of the outcomes. Provided the data is missing at random (MAR) or that the probability of missingness can be fully explained by observable data, this approach produces asymptotically unbiased estimates. To allow for the possibility that the MAR assumption may not hold, we will also use a second approach, pattern mixture models, in which the distribution of the outcome is assumed to follow a mixture of two distributions: one for those who complete follow up and another for those who do not.

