#### Primary outcome analyses

We will estimate the effect of the interventions on smoking cessation (biochemically verified 7-day point prevalence abstinence) at end-of-treatment and follow-ups (6, 9 and 12 months) using a longitudinal regression model implemented with generalized estimating equations (GEE) with robust standard errors [91, 92]. Specifically, we will regress smoking status on intervention group (BAT-CS vs. control) and potential covariates (cardiac rehabilitation attendance, cessation treatment outside of the study, other baseline variables will be included as covariates if they are both not balanced by randomization and are correlated with the outcome under consideration at *p* < 0.10 level) using binomial errors, a logit link function, and a working unstructured correlation to accommodate within-subject correlation.

We will use a series of longitudinal mixed effects regression models to estimate the effect of BAT-CS versus control on depressed mood (PHQ-9) at end-of-treatment and subsequent follow-ups, controlling for baseline depression, cardiac rehabilitation attendance, depression treatment outside of the study, and any other variables not balanced by randomization that are correlated with depressed mood at follow-ups at a modest *p* < 0.10 level. Models will include a subject-specific intercept to adjust for repeated measurements within participant over time. Modeling is done using a likelihood-based approach and thus makes use of all available data (on the intent to treat sample) without directly imputing missing outcomes, to produce consistent estimates of the regression parameters.

For primary outcomes (i.e., biochemically verified 7-day point prevalence abstinence and PHQ-9) we will conduct a per-protocol analysis (with parallel models to those described above) to assess differences between groups among those who completed a substantial number of treatment sessions. Per protocol will be defined completing at least four treatment sessions in both treatment groups.

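### The dropout weights are built from baseline data only, so the claim that they give unbiased estimates under MAR is too broad, chiefly for the abstinence analysis

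*Protocol article*

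**What the plan says.** The Missing data section of the protocol article sets an intention-to-treat analysis ("everyone randomized will be included in the final analysis") and names two approaches for testing robustness to missing data. The first is weighting in two steps. In step one, "the probability of missingness is modeled as a function of baseline covariates and baseline values of the outcome". In step two, "the inverse of the propensity scores (predicted probabilities of dropout from the first step) serve as weights in our regression model of the outcomes". The section then claims a property for these weights under either of two conditions: the data are MAR, or the chance of being missing is one that "can be fully explained by observable data, this approach produces asymptotically unbiased estimates". The second approach, pattern mixture models, is offered for the case where MAR fails.

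Under Primary outcome analyses, abstinence at the four follow-ups is analysed "using a longitudinal regression model implemented with generalized estimating equations (GEE) with robust standard errors", with an unstructured working correlation. PHQ-9 is analysed by a likelihood-based mixed model that "makes use of all available data (on the intent to treat sample) without directly imputing missing outcomes". The section on retention expects at least 80–85% follow-up, so up to 15–20% of assessments may be missing.

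**The concern.** MAR in a longitudinal trial means that missingness at a visit may depend on anything already observed, including outcomes at earlier follow-ups. Here that is smoking status and PHQ-9 at 12 weeks, 6 and 9 months. The dropout model lists none of these, and it does not list arm. The stated condition (MAR, or any observable data) is therefore wider than the condition the weights need.

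The gap is relevant in this trial. Its conceptual model links low mood to smoking, and people who return to smoking or whose mood worsens after the first week may well be the ones who leave. If they are, both the unweighted abstinence GEE and the weighted check could be off in the same direction. Agreement between them would then say little about robustness.

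**Working it through.** The plan gives no figure to reproduce, because the point concerns a stated property. The check has two parts.

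**1. Conditions side by side.** Write H(t) for everything observed before visit t, and B for the modelled baseline variables.
- MAR with dropout: P(drop out at t) depends on H(t), which contains B and earlier abstinence and PHQ-9.
- What baseline-only weights require: P(drop out at t) depends on B alone.

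The second condition implies the first, but not the reverse. So the sentence is false for any MAR mechanism that uses a follow-up outcome. B does include Baseline 2, taken one week after discharge just before randomization, with smoking status, cotinine, CO and PHQ-9 (Table 1). Changes in the first week can therefore enter the weights. Later ones cannot.

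**2. Large-sample illustration.** Simulation with 400,000 subjects, four visits and monotone dropout. The coefficients are assumptions, because the document gives none.
- Abstinence at visit t: logit = b_t − 0.25x + 1.0(s0 − 0.43) + u + 0.5·arm, with b = −0.75, −1.0, −1.2, −1.35. Here x and s0 are baseline variables and u is a subject effect with SD 1.5. True 12-month abstinence is 28.2% vs 35.7%, close to the protocol's 29% vs 37%.
- Dropout logit at the first visit: −3.5 + 0.2x − 0.3·s0. At later visits: (A) −2.9 + 0.3x − 0.6·s0; (B) −4.6 + 0.2x + 2.0·(smoking at last visit); (C) −4.8 + 0.2x + (smoking at last visit)·(0.9, plus 1.9 in control). All three are MAR.
- Weights: the inverse of the probability of being observed, from x and s0 only (baseline), or the product over visits of models that add arm, last abstinence and their interaction (sequential).

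Crude 12-month rates, control vs BAT-CS (difference in points):

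| Scenario (12-month retention) | Full data | Unweighted | Baseline weights | Sequential weights |
|---|---|---|---|---|
| A, baseline only (85%) | 28.2 vs 35.7 (7.6) | 28.7 vs 36.3 (7.6) | 28.2 vs 35.7 (7.6) | 28.2 vs 35.7 (7.6) |
| B, after smoking, equal arms (84%) | 28.2 vs 35.7 (7.6) | 29.6 vs 37.3 (7.7) | 29.2 vs 36.9 (7.7) | 28.2 vs 35.8 (7.6) |
| C, after smoking, stronger in control (84%; 75% vs 93%) | 28.2 vs 35.7 (7.6) | 30.8 vs 36.1 (5.3) | 30.5 vs 35.7 (5.3) | 28.2 vs 35.7 (7.6) |

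In B each arm's rate is about 1 point too high, but the difference barely moves. In C the difference is short by 7.6 − 5.3 = 2.3 points, and the baseline weights recover essentially none of it. The four-visit odds ratio under working independence is 1.34 with baseline weights against 1.42 in full data.

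Two other arm-differential set-ups gave shortfalls of 5.8 − 4.9 = 0.9 points (per-visit dropout 3% after abstinence, and 12% vs 7% after smoking in control vs BAT-CS) and 7.7 − 5.0 = 2.7 points. A harsher variant, with retention of 62% vs 87% (75% overall, below the protocol's expectation), gave 7.4 − 3.8 = 3.6 points.

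**3. The model actually planned.** The figures above are crude rates or working independence. The planned GEE has an unstructured working correlation, which borrows from earlier abstinence.
- Using the 3%, 12% and 7% dropout rates with a separate outcome model, the four-visit odds ratio was 1.32–1.33 in full data, 1.27–1.28 under working independence and 1.31–1.32 with the unstructured structure. Most of the bias went.
- With dropout depending on earlier observed mood, more strongly in control (retention 76% vs 83%), the unstructured GEE gave 9.8 points against a true 11.4, and an odds ratio of 1.44 against 1.52. It gave the same figures unweighted and with baseline-only weights. Sequential weights that included earlier mood gave 11.3.

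**The case against.** A reader might infer more than the document supports: that the abstinence model has no protection against MAR dropout, that the weighting is its only safeguard, and that the treatment effect will be biased by a known amount. Each of these fails.
- The unstructured working correlation uses earlier abstinence. It removed most of the bias when dropout followed smoking, although GEE carries no general guarantee under MAR.
- Pattern mixture models are planned as a second, separate check.
- Baseline 2 supplies smoking and PHQ-9 values that vary between participants, so the baseline outcome is not a constant even though all were daily smokers before admission.
- Bias in the between-arm difference appeared only when dropout after smoking or low mood differed by arm. Nothing in the document predicts that: contact time and incentives are matched across arms.
- The bias is modest beside sampling error. With 162 per arm and rates of 29% and 37%, the standard error of a 12-month difference is √(0.29×0.71/162 + 0.37×0.63/162) = 0.052, about 5 points.
- The PHQ-9 model is likelihood-based. If correctly specified, it handles dropout that depends on earlier PHQ-9 scores without help from the weights.

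It can also be said that an article leaves the detail of a dropout model to the full analysis plan. That does not answer the point, because the article states both the predictors and the property, and the two do not fit. What stands of the objection limits the consequence. It does not rescue the sentence.

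**Conclusion.** The claim of asymptotic unbiasedness is wrong as written. It holds only if dropout depends on the modelled baseline variables alone and the dropout model is correct, which is narrower than MAR. The consequence falls mainly on the abstinence analysis. There the GEE cannot use earlier PHQ-9, and the baseline-weighted sensitivity analysis can reproduce the primary model's bias instead of exposing it.

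The size cannot be fixed from the document. Under the assumed mechanisms, the between-arm difference is almost unaffected if dropout after smoking is equal across arms. Crude 12-month differences are off by about 1 to 3 points when it is not, and by more under heavier loss than the protocol expects. For the planned unstructured GEE, the bias is small when dropout follows smoking; in the one mood-driven illustration it was 11.4 − 9.8 = 1.6 points. This is a correctable fault in a robustness analysis, not evidence that the primary result will mislead.

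**What to change.** For the weighted analysis, model the probability of being observed at each visit from arm, baseline variables (including Baseline 2), and previously observed abstinence and PHQ-9, with arm interactions. Multiply the inverse probabilities over visits. State that the weights are inverse probabilities of being observed, since the text refers to probabilities of dropout. Run the visit-weighted GEE under working independence, the setting in which the sequential weights above were shown to recover the full-data result; visit-specific weights combined with a non-diagonal working correlation are not valid in general. Multiple imputation by arm with the same variables is an acceptable alternative.

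Restate the MAR sentence so that unbiasedness is claimed only when missingness is explained by the variables in the weight model and that model is correct. Keep the pattern mixture models for departures from MAR.

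The data are already collected at every follow-up through 12 months (Table 1). The cost is wording and some programming. The downside is possibly more variable weights, and so somewhat less precision in this sensitivity analysis.
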